### Statistical analyses

Treatment evaluation will be performed on the principle of intention to treat. Statistical analyses will be conducted using SAS version 9.3 software (SAS Institute, Cary, NC, USA). The present study is a standard two-arm equality trial; therefore, all statistical tests will be two-sided and maintained at a 5% significance level. Demographics and baseline characteristics of all randomised participants will be summarized for each group as well as overall. Continuous variables will be reported as mean ± SD. Categorical variables will be reported as numbers (%).

Simple χ^2^ analyses will be used to evaluate the main treatment effect on the proportion of participants adherent to health behaviours at end of the intervention period, with estimation of relative risks, 95% confidence intervals and two-sided *P*-values. We hypothesise that the proposed intervention will change the proportion of participants adherent to recommended healthy behaviour guidelines at 6 months after randomisation by at least 25% compared with the control group. Multiple regression analysis appropriate for binary and continuous outcome measures will be conducted to evaluate the treatment effects, adjusting for important confounding factors at baseline. All analyses for secondary outcomes will be exploratory.

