### Outcome assessments

Assessments will be conducted at baseline and 6 months postrandomisation (see Figure 
1). Baseline assessments will involve an explanation of study procedures, signed consent and collection of demographic details. Participant-reported primary and secondary outcomes will then be collected, followed by physical measurements, including height, weight, waist and hip circumference, blood pressure and blood cholesterol. The baseline assessment concludes with randomisation and assignment of participants to the respective study groups.

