### Sample size

One hundred twenty participants (sixty per group) will provide at least 80% power at the 5% level of significance (two-sided) to detect an absolute difference of 25% between the two groups, in the proportions of participants adherent to recommended healthy behaviour guidelines (that is, not smoking, low alcohol consumption, fruit and vegetable intake and engaging in physical activity) at 6 months after randomisation.

The sample size calculation was based on data from the EPIC-Norfolk Prospective Population Study, in which the investigators used a composite health behaviour score to determine the relationship between lifestyle and total mortality by cause in adults between 45 and 79 years of age living in the general community
[27]. Given our population of people with established CHD, we estimate that 30% to 40% of our sample will be adherent to healthy behaviour guidelines at baseline
[27].

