### Randomisation and blinding

Following baseline data collection, eligible and consented participants will be randomised to either the intervention group or the control group in a 1:1 ratio. The randomisation sequence will be generated by using a computer program in blocks of six and will be overseen by the project statistician and unavailable to outcome assessors. Randomisation will be stratified according to smoking status (smoker vs. nonsmoker) to help balance baseline health behaviour scores. Allocation will be concealed in consecutively numbered, opaque sealed envelopes. Owing to the nature of the intervention, participants will be aware of the group to which they have been assigned; however, at follow-up, outcome assessors will be blinded to the treatment allocation.

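### The main analysis is an unadjusted chi-square that uses neither the baseline health behaviour score nor the smoking stratum: a valid test, but one that gives up efficiency in a design with no spare power

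*Protocol article*

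**What the plan says.** All references are to the Protocol article.

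- **Main test** (Statistical analyses): "Simple χ^2^ analyses will be used to evaluate the main treatment effect on the proportion of participants adherent to health behaviours". Relative risks, 95% confidence intervals and two-sided P-values accompany it. No covariate or stratification factor is named for this test.
- **Second analysis** (same section): "Multiple regression analysis appropriate for binary and continuous outcome measures will be conducted to evaluate the treatment effects, adjusting for important confounding factors at baseline". The factors are not listed, and this regression is not the one assigned to the main treatment effect.
- **Baseline data** (Outcome assessments): at the baseline visit, which ends with randomisation, "Participant-reported primary and secondary outcomes will then be collected". The four components of the composite score are therefore known for each participant before allocation.
- **Stratification** (Randomisation and blinding): "Randomisation will be stratified according to smoking status (smoker vs. nonsmoker) to help balance baseline health behaviour scores". Being a nonsmoker is one of the four points of the score (Primary outcome).
- **Sample size**: 60 per group for at least 80% power, two-sided 5%, "to detect an absolute difference of 25% between the two groups". The only rate given is for baseline: "we estimate that 30% to 40% of our sample will be adherent to healthy behaviour guidelines at baseline". No dropout rate or inflation is stated.

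**The concern.** The stratification is justified by its effect on baseline health behaviour scores, so the plan itself treats those scores as worth balancing. The main test then ignores them. If adherence at baseline predicts adherence at 6 months, an analysis that conditions on it has more power from the same participants. Stratifying on smoking handles only one of the four components. Differences between arms in physical activity, alcohol intake, and fruit and vegetable intake are left to chance, and the crude comparison does not use the information on them.

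At stake is the chance of detecting the planned 25-point difference. With power at its nominal target under complete follow-up, any loss of participants takes it below 80%. The baseline score is a source of precision that is already paid for.

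**Working it through.** **Inputs from the article.** 60 per arm, 1:1, two-sided 5%, difference 25 points. No 6-month control rate is given, so the baseline range of 30% to 40% is taken as the control rate.

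**Inputs assumed.** The correlation r between baseline and 6-month adherence (range 0 to 0.5), loss to follow-up (10%), and the share of smokers (15%). None of these is in the article.

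**Step 1: reproduce the plan's power.** With P the mean of the two proportions p1 and p2, and d their difference,

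power = Φ{ [ d√n − 1.96 √(2P(1−P)) ] / √( p1(1−p1) + p2(1−p2) ) }.

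For 35% versus 60%: d√n = 0.25 × √60 = 1.936. With P = 0.475, 1.96 × √(2 × 0.475 × 0.525) = 1.384. The denominator is √(0.2275 + 0.24) = 0.684. So (1.936 − 1.384)/0.684 = 0.808, and the power is 79.0%.

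| Control vs intervention | Power at 60 per arm | n per arm for 80% |
|---|---|---|
| 30% vs 55% | 79.9% | 61 |
| 35% vs 60% | 79.0% | 62 |
| 40% vs 65% | 79.0% | 62 |

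The unpooled formula needs 58 to 59 per arm, so the stated figure reproduces, but with no margin. With an assumed 10% loss (54 per arm), power at 35% versus 60% is 74.6%.

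**Step 2: adjust for baseline, by approximation.** A covariate with correlation r to the outcome reduces the residual variance by the factor 1 − r². The effective n per arm is then 60/(1 − r²), which goes into the same formula at 35% versus 60%:

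| Assumed r | Effective n per arm | Power |
|---|---|---|
| 0 | 60.0 | 79.0% |
| 0.2 | 62.5 | 80.7% |
| 0.3 | 65.9 | 82.8% |
| 0.4 | 71.4 | 85.7% |
| 0.5 | 80.0 | 89.4% |

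With 54 per arm and r = 0.4, the effective n is 54/0.84 = 64.3 and power is 81.8%, against 74.6% unadjusted.

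**Step 3: check by simulation.** 4,000 trials per setting compared the chi-square with logistic regression on the baseline score; r is the correlation between binary adherence at baseline and at 6 months.

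| r (approx.) | Control rate | Chi-square | Adjusted |
|---|---|---|---|
| 0 | 30% | 81.9% | 81.4% |
| 0 | 40% | 81.5% | 80.0% |
| 0.32 | 30% | 81.0% | 85.1% |
| 0.33 | 40% | 80.4% | 83.8% |
| 0.48 | 30% | 79.9% | 90.3% |
| 0.49 | 40% | 80.6% | 90.7% |

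The simulation agrees with the approximation and shows the small cost of adjusting when r is zero. Under no treatment effect the chi-square rejected in 5.3% and 5.5% of trials at r about 0.32 and 0.49, and the adjusted test in 4.7% and 5.0%.

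**Step 4: the smoking stratum alone.** 6,000 trials per setting compared the chi-square with a Mantel-Haenszel test stratified by smoking, with 15% smokers. Where smokers' adherence equals, is half of, or is a quarter of nonsmokers', the gain is 0, 0.1 and 0.8 points at a 30% control rate, and 0, 0.3 and 1.7 points at 40%. Under no effect, the chi-square's rejection rate was 4.9% where smokers' adherence was half that of nonsmokers, and 4.1% where it was one tenth. Ignoring the stratum therefore makes the test conservative only in an extreme case.

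**The case against.** The best defence is that nothing here is wrong in the strict sense. A chi-square on two randomised proportions controls its error rate, chance imbalance is already allowed for in its confidence interval, and it is the test on which the sample size rests. All of that stands. A reader might infer from the unused stratum that the test is invalid or the estimate biased; the calculations do not support this.

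The second defence is that the gain depends on a correlation the article does not report, and there are reasons it could be modest. Participants are screened during hospital admission, may still be in hospital at baseline, and are all then offered rehabilitation intended to change the measured behaviours. This also stands. It is why the range must start at zero, and why it cannot be claimed as fact that 6-month adherence depends strongly on baseline adherence.

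The third defence is that an adjusted regression is already planned. This is only a partial answer, because the main treatment effect is assigned to the chi-square. That the regression's covariates are unnamed is not a fault to press: a condensed article may leave the list to an analysis plan that is not shown. Nor do the documents support a complaint that odds ratios would conflict with the planned relative risks. They name neither a logistic model nor an odds ratio.

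**Conclusion.** The point holds as one of efficiency. The article fixes an unadjusted main test while collecting, before randomisation, the variable most likely to sharpen it. For assumed correlations of 0.2 to 0.5 at 35% versus 60%, power with adjustment is about 81% to 89%, against about 79-80% without. At zero correlation there is nothing to gain and about 1 point to lose. If 10% are lost and r is 0.4, adjustment makes the difference between about 75% and about 82%. Nearly all of this comes from the baseline score; the smoking stratum by itself contributes between 0 and about 1.7 points under the assumptions shown.

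This does not make the planned analysis unsound, and the trial could be reported validly as written. It is a free improvement worth making, and not a condition for the trial to proceed. The size rests on the assumed correlation and on using the baseline adherence range as the 6-month control rate.

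**What to change.** In Statistical analyses, make the primary analysis one prespecified regression of 6-month adherence on arm, baseline composite health behaviour score (or baseline adherence) and smoking stratum. Report the marginal relative risk and the risk difference with 95% confidence intervals, for example from a modified Poisson model or a logistic model followed by standardisation. Keep the simple chi-square as a supporting analysis, so that the link to the sample size calculation remains visible. Hospital need not be added, since randomisation is not stratified by it.

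The cost is a change of analysis wording. Both covariates are already collected, and no extra participants or visits are needed. The article describes the trial as open for recruitment, so the change should be made and dated before any outcomes are compared by arm.

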## Discussion

The Text4Heart trial will evaluate a comprehensive mHealth CR intervention to improve adherence to lifestyle behaviours. To the best of our knowledge, this is the first mHealth study to assess multiple behaviours using a composite score and one of the first to evaluate a comprehensive mHealth self-management intervention in adults with CHD. The protocol, in accordance with the SPIRIT statement, incorporates findings from recent mHealth systematic reviews with the aim of adding quality evidence to the body of literature.

Common criticisms have been voiced regarding mHealth research designs and trial descriptions
[41,53]. Few adequately powered randomised controlled trials have been completed to date. Intervention duration and follow-up assessments are often not long enough, as it takes approximately 6 months for participants to adopt new behaviours
[54]. The Text4Heart trial has been developed with these concerns in mind, and therefore we have incorporated a randomised controlled trial design with a 6-month follow-up period.

Many mHealth studies also fail to fully describe their interventions, in particular the behaviour change theory or BCTs used, if any, and the evidence behind the content of the intervention
[25,53]. mHealth studies often offer insufficient explanation of the intervention for its design to be replicated
[25]. This is a particular concern because mHealth technology changes rapidly, and it is important to know which aspects of an intervention worked and which did not. The Text4Heart study protocol describes the intervention in full, including the theoretical framework and examples of SMS and Internet content. The intervention incorporates knowledge learned from previous mHealth research and has involved the target audience in the content development stage of the intervention.

On the basis of earlier results, it is evident that the CHD population in New Zealand is interested in mHealth CR and is able to use the related technology
[20,55]. If effective, the trial has the potential to be implemented in a CR setting and to be used as a model for other disease prevention and self-management programs. The intervention could easily be augmented to provide opportunities for clinicians to engage in two-way communication with patients regarding their lifestyle behaviours, as well as clinical outcomes such as monitoring blood pressure and weight. This study will provide data on the potential of mHealth to improve patient care.

## Trial status

The trial is currently open for recruitment.

## Abbreviations

BCT: Behaviour change technique; BIPQ: Brief Illness Perception Questionnaire; CHD: Coronary heart disease; CR: Cardiac rehabilitation; CVD: Cardiovascular disease; GLTPAQ: Godin Leisure Time Physical Activity Questionnaire; MMAS: Morisky 8-item Medication Adherence Scale; HADS: Hospital Anxiety and Depression Scale; SCT: Social cognitive theory; SMS: Short messaging service.
